## Abstract

In this 12-month randomized active-controlled clinical trial, we compare two post-treatment instructions for silver diamine fluoride (SDF) therapy in arresting dentine caries. The trial will include at least 254 kindergarten children with active dentine caries. The children will be randomized into two groups and receive a 38% SDF solution applied topically to their carious lesions. Children in Group A will rinse immediately, whereas those in Group B will refrain from rinsing, eating, and drinking for 30 min. One trained examiner will perform the dental examination at baseline and every six months. The primary outcome measurement will be the proportion of caries lesions that become arrested at the 12-month examination. Potential confounding factors and parents’ satisfaction with SDF therapy at baseline and after 12 months will be collected using parental questionnaires. This trial will provide evidence-based information for clinical practitioners to give post-treatment instructions for SDF therapy. This study is registered at ClinicalTrial.gov (USA) (registration number: NCT05655286).

## 1. Introduction

Early childhood caries (ECC) is defined as the presence of one or more primary teeth with decayed, missing (due to caries), or filled surfaces in a child under the age of six (71 months) [1]. A review based on 88 countries shows that the mean ECC prevalence for children aged 3–5 years is 57% [2]. ECC is more common in children from low-income families [3] who cannot afford the restorative dental treatment or do not have access to dental care [4]. According to the global burden of dental disease in 2019, 62.9 million children had decayed teeth, which was attributed to global sociodemographic inequality [5].

In Hong Kong, almost half (46%) of the children aged 3–5 years suffer from ECC, and most of the decayed teeth (95%) remain unrestored [3]. When untreated ECC continues to progress, it can lead to dental pain and systemic infection, negatively affecting children’s quality of life [6]. Currently, the Hong Kong government mainly implements the oral health promotion program by delivering free oral health education materials to kindergarten teachers and parents to manage ECC. No government-subsidized treatment program was provided for young children to treat ECC.

Managing ECC through low-cost and minimally invasive methods is vital to relieve the huge global burden of untreated ECC. Nowadays, silver diamine fluoride (SDF) is regarded as a viable therapy alternative for arresting dentine caries due to its effectiveness, affordability, and accessibility [7]. SDF is available commercially for dental use at various concentrations in some counties [8], including 3.8%, 10%, 12%, 30%, 38%, etc. [9]. SDF is generally used for ECC treatment at 38%, which contains 253,870 ppm silver and 44,800 ppm fluoride ions.

Laboratory studies have confirmed the mechanism of SDF for caries control, including silver’s antibacterial effect, fluoride’s remineralization effect, and the ability to inhibit dentine collagen degradation [9]. A clinical trial on SDF for caries arrest in young children showed no serious adverse events [10]. A systematic review showed that SDF could arrest approximately 80% of treated lesions [11]. In addition, SDF therapy is cost-effective, with the material costing less than one USD per application, making it affordable for children from low socioeconomic families [7,12]. Because SDF treatment produces minimal aerosols, it is considered an alternative to caries management during and after the COVID-19 era [8].

Although SDF is effective in arresting ECC, it has some drawbacks, including a metallic or bitter taste. Some children commented that SDF’s taste and smell are unfavorable and unacceptable. They want to rinse or spit out the excessive SDF after treatment if allowed. The published clinical protocol for the UCSF (University of California, San Francisco) dental clinics stated that clinicians should rinse the treated carious lesion with water after SDF treatment [13]. However, the in vitro results of micro-computed tomography indicated that water rinsing could reduce the radiopacity of SDF-treated decayed teeth, possibly due to the reduced SDF precipitation on the decayed teeth [14].

There is no post-treatment instruction available in the clinical recommendations for SDF by the American Academy of Pediatric Dentistry (AAPD) [15]. We searched the published clinical trials on SDF therapy in PubMed. Some publications mention that children refrained from eating and drinking for 30 min [13,16] or 60 min [17,18] after SDF therapy. Some studies do not mention the post-treatment instructions for SDF treatment [19,20], whereas a few studies state that the SDF-treated lesions were rinsed immediately [21,22]. There is no published study in PubMed investigating SDF’s caries-arrest effectiveness with various post-treatment protocols.

Recently, the World Health Organization (WHO) Collaborating Centre expanded the WHO list of essential medicines and added SDF to a new category in 2021 [12]. Therefore, the evidence-based clinical guideline for SDF treatment is crucial for dental practitioners, dental educators, and dental public health workers. In this study, we aim to compare the effectiveness of the various post-treatment instructions for SDF application in arresting dental caries. The proposed study’s results will provide scientific-based evidence regarding the post-treatment SDF protocol.

## 2. Methods/Design

This study is a prospective, parallel, blind, randomized controlled trial with two arms, following the SPIRIT (Standard Protocol Items: Recommendations for Interventional Trials) [23].

### 2.1. Objective

The objective of this randomized clinical study is to compare the effectiveness of the two post-treatment instructions after application of 38% SDF every 6 months over a 12-month period in arresting dental caries among preschool children.

### 2.2. Hypothesis

The null hypothesis of this study is that there is no difference in the caries-arrest effectiveness of the two post-treatment instructions after application of 38% SDF every 6 months at the 12-month follow-up.

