### 2.10. Sample Size Calculation

According to the published studies, approximately 70% of active dentine caries in primary teeth were halted after 38% SDF treatment [27]. Clinical significance would be defined as an absolute difference of 10% in the arrested caries rate between the groups. A two-tailed test with a statistical significance of 0.05 (α = 0.05) and a power of 80% (β = 0.2) will be set. The Sealed Envelope website will be used to calculate the sample size (https://www.sealedenvelope.com/, accessed on 1 November 2022). At least 708 active carious tooth surfaces in total (354 per group) are needed.

The anticipated intraclass correlation coefficient for the caries data at the tooth surface level within a child is 0.13. Following the results of the published study, the mean number of decayed tooth surfaces per child was 5 at baseline. According to the sample size calculation for a multilevel statistical model, the estimated design effect is 1.52. Hence, at least 1077 decayed tooth surfaces are needed. After 12 months, the anticipated dropout rate is approximately 15%. Therefore, at least 1267 tooth surfaces and 254 children in total (127 per treatment group) need to be recruited at baseline.

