## 3. Discussion

SDF treatment is a simple, affordable, and effective treatment for caries control in children. The US Food and Drug Administration (FDA), the AAPD, and the WHO have regarded it as an essential strategy for oral health management to address the burden of dental caries [12,28,29]. Recently, SDF treatment has been adopted in community-based dental programs to manage ECC in many countries or regions, including Argentina, Australia, Brazil, Hong Kong in China, Egypt, Finland, India, Japan, Mongolia, South Africa, the United Kingdom, the United States, etc. However, a review shows that the guidelines for SDF vary significantly in different countries, and there is still no agreement between clinicians regarding the SDF treatment protocol due to limited supporting evidence [8].

A study shows that SDF therapy is a child-friendly method to treat ECC in the kindergarten setting [30]. In Hong Kong, a territory-wide dental outreach project using SDF for caries control has been implemented in 1000 kindergartens (https://www.jccohp.hku.hk, accessed on 1 November 2022) since 2020. This project was funded by a non-governmental organization and performed by the Faculty of Dentistry at the University of Hong Kong, aiming to improve the oral health of kindergarten children. The children are instructed not to eat or drink for 30 min after receiving the SDF treatment. The 30 min are arbitrarily set in order to allow more contact time between SDF and the carious lesions. It is supposed that the prolonged contact time enhances the effectiveness of SDF to arrest caries, but the evidence is lacking.

The instruction of no eating or drinking for 30 min requires teachers to monitor the SDF-treated children. This is difficult to implement when the service time is near lunch or break time. Moreover, the instruction sometimes disturbs the school schedule. In addition, SDF’s unpleasant taste may be alleviated if no restriction about refraining from rinsing, drinking, and eating is imposed. A lack of post-treatment instruction may be desirable and practical if the caries-arrest effectiveness is not diminished. However, questions remain about whether a lack of post-treatment instruction may deteriorate SDF’s caries-arrest efficacy. The results of this clinical trial will give an evidence-based suggestion for post-treatment instruction in SDF therapy.

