The strength of this study includes a sufficient sample size, which generates adequate study power. This study protocol describes the specific and detailed procedure for conducting a prospective, blinded, randomized clinical trial. Any materials and equipment used are explicitly listed. The protocol of procedures is based on the published peer-reviewed articles, and the method steps are reproducible. A limitation of this trial is that the participating children cannot be blind to the group intervention because they need to perform rinsing or refrain from rinsing according to their treatment allocation. Nevertheless, the awareness of the treatment allocation among preschool children is unlikely to influence the study outcomes. Regarding the external validity, this clinical trial will be conducted in kindergarten children. Therefore, the results may not be translatable to other age groups.

This randomized controlled clinical trial will provide evidence on whether it is necessary to give a post-SDF treatment instruction to refrain from eating and rinsing for 30 min. The results of this study will be beneficial for dental practitioners and dental public health workers in the adoption of SDF for caries control in young children.

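### The no-difference test can detect a loss of arrest, but a non-significant result cannot show that arrest is undiminished without the 30-minute restriction, and the article gives no rule for that conclusion

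*Protocol article*

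**What the plan says.** The Methods describe a difference trial throughout. The objective (section 2.1) is to "compare the effectiveness of the two post-treatment instructions after application of 38% SDF every 6 months". The null (section 2.2) is that "there is no difference in the caries-arrest effectiveness of the two post-treatment instructions". Section 2.10 specifies "A two-tailed test with a statistical significance of 0.05 (α = 0.05) and a power of 80" per cent, takes from earlier work that "approximately 70% of active dentine caries in primary teeth were halted after 38% SDF treatment", and states: "Clinical significance would be defined as an absolute difference of 10% in the arrested caries rate between the groups". Section 2.11 sets 0.05 for all tests and lists chi-square, logistic and generalized estimating equation (GEE) analyses.

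The Discussion (section 3) describes the practical use of the result: "A lack of post-treatment instruction may be desirable and practical if the caries-arrest effectiveness is not diminished". It asks "whether a lack of post-treatment instruction may deteriorate SDF’s caries-arrest efficacy", and closes by promising "evidence on whether it is necessary to give a post-SDF treatment instruction to refrain from eating and rinsing for 30 min".

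The article gives no non-inferiority or equivalence hypothesis, no margin and no confidence-interval rule, and it does not say how a non-significant result will be read.

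**The concern.** The practical decision runs in one direction: the easier instruction can be adopted if arrest does not suffer. Failing to reject a no-difference null does not show that. It is compatible with no loss, and also with a loss that the trial was too imprecise to detect.

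Some loss is plausible on the article's own account. The Introduction cites in vitro work in which rinsing lowered the radiopacity of treated teeth, possibly through less SDF precipitation. The Discussion describes the 30-minute restriction as the current instruction in an outreach project covering 1000 kindergartens, so a null result could influence practice widely. The Discussion also calls the sample size sufficient and the power adequate, which may encourage readers to take a null result as reassurance.

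**Working it through.** **Inputs (section 2.10).** Arrest 70%; difference 10 points; two-sided alpha 0.05; power 80%; intraclass correlation 0.13; 5 surfaces per child; dropout 15%; 254 children.

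**1. The plan's own sample size.** (1.960 + 0.842)² = 7.849.
- Surfaces per group, 70% v 60%, unpooled variance: 7.849 × (0.21 + 0.24) / 0.10² = 353.2, so 354 per group and 708 in total. This matches.
- Design effect: 1 + (5 − 1) × 0.13 = 1.52. 708 × 1.52 = 1076.2, so 1077.
- Dropout: 1077 / 0.85 = 1267. 1267 / 5 = 253.4, so 254 children. This matches.

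The arithmetic is sound for a difference test.

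**2. Effective size at 12 months.** 254 × 0.85 × 5 / 2 / 1.52 = 355 surfaces per group.

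**3. Chance of a non-significant result when there is a true loss (Group B at 70%).** SE = √[(0.21 + pA(1 − pA)) / 355]; power ≈ Φ(loss / SE − 1.96).

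| True loss in Group A | SE | Power | Non-significant |
|---|---|---|---|
| 5 points | 0.0351 | 0.30 | about 70% |
| 8 points | 0.0354 | 0.62 | about 38% |
| 10 points | 0.0356 | 0.80 | about 20% |

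**4. What a non-significant result would leave open.** The 95% CI for the loss is the observed loss ± 1.96 × SE, with Group B observed at 70%.

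| Observed loss | p | 95% CI for the loss (points) |
|---|---|---|
| 3 points | 0.39 | −3.8 to 9.8 |
| 4 points | 0.25 | −2.9 to 10.9 |
| 5 points | 0.15 | −1.9 to 11.9 |
| 6 points | 0.09 | −0.9 to 12.9 |

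All four are non-significant. Only the first excludes a 10-point loss.

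**5. What a confidence-interval rule would need.** The article gives no margin, so the margin is an assumption here and a range is shown. With 70% arrest in both groups, one-sided 2.5% and 80% power, surfaces per group = 7.849 × 0.42 / margin². Power at the planned size = Φ(margin / √(0.42/355) − 1.96), with √(0.42/355) = 0.0344.

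| Margin | Surfaces per group | Children | Power with 254 children |
|---|---|---|---|
| 10 points | 330 | 237 | about 83% |
| 8 points | 516 | 370 | about 64% |
| 5 points | 1319 | 944 | about 31% |

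For 10 points: 660 × 1.52 = 1003.2, so 1004; 1004 / 0.85 = 1181.2, so 1182; 1182 / 5 = 236.4, so 237.

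If Group A is truly 2 points worse (68% v 70%) and the margin is 10 points, power = Φ(0.08 / √(0.4276/355) − 1.96), about 63%.

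**The case against.** The difference design has real support. Objective, null, two-tailed test and 10-point target agree with one another. The Discussion calls the 30 minutes arbitrary, says evidence for longer contact is lacking, and asks whether leaving out the instruction worsens arrest. A two-sided test answers that question when the loss is large enough. The 20% miss rate at 10 points is simply the planned beta, and the 5- and 8-point losses are smaller than the difference the plan calls clinically significant. Reading rules are also often left to a full protocol or SAP, which is not shown. All this stands, and it means that the primary test need not be replaced.

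A reader might infer three stronger things that the document does not support:
- *That a null result will be reported as proof of no loss.* The article never says how such a result will be read. The text supports only that it could be.
- *That the plan already contains a non-inferiority margin.* Section 2.10 names 10 points as a clinically significant difference. It does not say that a loss just under 10 points is acceptable.
- *That the primary hypothesis must be changed to non-inferiority at no cost.* Section 2.12 has registration in December 2022 and recruitment from February 2023. Replacing the primary hypothesis at that stage is itself open to criticism, and the planned number suffices only under favourable assumptions.

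What the objection does not remove is the promise in the Discussion to inform whether the instruction is necessary. The hypothesis and test that the article does fix cannot support a negative answer through non-significance alone.

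**Conclusion.** The concern holds as a gap between the fixed test and one of the conclusions that the article wants to be able to draw. It is not an error in the test or in the sample size. The test can show a loss, but its non-significance cannot show that there is none. With about 355 effective surfaces per group, an observed loss of 4 to 6 points would be non-significant and yet leave a loss above 10 points within the 95% CI.

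These figures rest on the plan's assumptions of 70% arrest in Group B, a design effect of 1.52 and 15% dropout. The 83% power further assumes a 10-point margin and exactly equal arrest. It drops to about 63% if Group A is truly 2 points worse, and to 64% or 31% with a margin of 8 or 5 points.

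**What to change.** Keep the two-sided primary test and add the following, before outcome data are seen:

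1. Arrest is concluded to be undiminished only if the lower limit of the two-sided 95% CI for Group A minus Group B in arrest proportion lies above minus the margin. The interval must allow for clustering. The GEE approach in section 2.11 can provide this if it reports a difference in proportions.
2. A margin with a stated justification. The plan's 10 points is the natural candidate, but the sponsor must argue why a smaller loss would be acceptable.
3. The result for all randomised children and for compliant children. Section 2.8 already has compliance recorded at each treatment visit. The compliant set is smaller, so its power will be lower.
4. A sentence stating that non-significance alone will not be read as equal effectiveness. This is the minimum change and needs no margin.

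Cost: justification of the margin, a dated amendment and a registry update, since recruitment has started. No additional children are needed at a 10-point margin with equal arrest. A tighter margin would mean more children (about 370 at 8 points, 944 at 5) or accepting the lower power.

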### 2.3. Setting

This clinical trial will be implemented in kindergartens in Hong Kong, where the fluoride concentration in the water supply has been 0.5 ppm since 1988. An invitation letter will be issued to the kindergarten principals to explain this trial’s objective and procedures. After receiving confirmation of participation from the principals, the children’s parents will receive an information sheet and consent through the kindergartens (Supplemental Material S1). In the information sheet, information about the study’s aim, follow-up time, anticipated sample size, the potential benefit and the common side effects of the SDF treatment, the allocation of treatment groups, and the expected treatment outcome will be included. Only the children whose parents read the information sheet and signed the parental consent form will be involved in the dental examination and SDF treatment. Figure 1 shows the CONSORT flow diagram.

The timeline of the study enrolment, intervention, and assessment is shown in Table 1.

### 2.4. Participants

Children in kindergartens will be invited to take part in this clinical trial. The inclusion criteria will be children who (1) have written parental consent, (2) are generally healthy, and (3) have at least one soft dentine caries according to the WHO criteria. Children who (1) are unwilling to accept oral examination or treatment, (2) have a significant systemic disease or take long-term medication that may affect oral health such as children with autoimmune disease, etc., or (3) have developmental dental anomalies such as amelogenesis imperfecta are excluded. Teeth with signs or symptoms of irreversible pulpitis or non-vitality will be excluded. Caries surfaces that were treated with a crown or restoration or arrested will also be excluded.

### 2.5. Recruitment and Examination

#### 2.5.1. Recruitment

A dentist ([name]) will be trained and calibrated by an expert ([name]) before the trial. The dentist will screen all children with parental consent in the participating kindergartens. The study children will be instructed to lie on a table and be clinically investigated. The dental examination will be conducted using visual inspection combined with tactile inspection. The visual inspection will be conducted with the aid of a disposable dental mirror mounted on the handle, which is equipped with intra-oral light-emitting diode lighting (MirrorLite, Kudos Crown Limited, Hong Kong SAR, China), and the tactile inspection will be performed using a 0.5 mm WHO Community Periodontal Index (CPI) ball-ended probe (405/WHO probe, Otto Leibinger, Muhlheim, Germany). No dental radiograph examination will be conducted. The children’s dental caries and oral hygiene status will be recorded.

#### 2.5.2. Assessment of Tooth Status

The WHO-recommended criteria for caries diagnosis will be adopted [24], and the number of decayed, missing (due to caries), and filled tooth surfaces (dmfs) will be recorded. Five surfaces of each posterior tooth and four surfaces of each anterior tooth will be thoroughly checked. Additional information, including discoloration, hypermobility, missing not due to caries, and presence of an abscess, will also be recorded.

The information about the recruited carious tooth surfaces will be recorded at baseline and at the time of each follow-up as follows: (1) caries activity status (active/arrested), (2) extent of caries lesion (ICDAS codes 5 and 6), and (3) presence of dental plaque (yes/no). The tooth surface will be diagnosed as active if any softened area on the caries lesion is detected through probing. When the entire caries lesion is detected as hard via probing, it will be recorded as arrested caries. The extent of dentine caries lesions will be assessed following ICDAS criteria [25], using codes 5 (distinct cavities) and 6 (extensive cavities). For those with filled or non-vital teeth at the follow-up, the carious lesions will be regarded as ‘failure’ or ‘active’. Table 2 shows the codes for the assessment of carious lesions (tooth surface level).

#### 2.5.3. Recording oral Hygiene

The visible plaque index (VPI) will be adopted for assessing children’s oral hygiene. The six index teeth’s buccal and lingual surfaces (55, 51, 63, 71, 75, and 83) will be assessed, and the presence of visible plaque (yes/no) will be recorded. The same examiner will conduct the dental examination using the same methods and equipment at the baseline visit and at each follow-up visit. The VPI value of each child will be calculated as a percentage of the total number of tooth surfaces with dental plaque to the total number of tooth surfaces checked.
$$\mathrm{VPI}\;\mathrm{value}=\frac{\mathrm{number}\;\mathrm{of}\;\mathrm{tooth}\;\mathrm{surfaces}\;\mathrm{with}\;\mathrm{dental}\;\mathrm{plaque}}{\begin{array}{c} \mathrm{number}\;\mathrm{of}\;\mathrm{tooth}\;\mathrm{surfaces}\;\mathrm{with}\;\mathrm{dental}\;\mathrm{palque}\\ +\mathrm{number}\;\mathrm{of}\;\mathrm{tooth}\;\mathrm{surfaces}\;\mathrm{without}\;\mathrm{dental}\;\mathrm{palque} \end{array}}\times 100\%$$

Regarding the dental caries and oral hygiene assessment, duplicate examinations on approximately 10% of the recruited children will be conducted to assess the examiner’s intra-reliability at each visit.

